### Randomisation and allocation concealment

Block randomization will be performed using Matlab to produce computer-generated random codes that are stratified according to key clinical indicators and demographic variables, including RRS, CDRS, sex and age. Block randomization will be conducted by individuals ([name], [name]) who will not share rumination scores, be providing therapy, or conducting independent assessments and will therefore be independent of the assessment and treatment staff. After each of four waves, the effect of randomization on age, sex distribution, RRS score, and proportion randomized to each arm are evaluated, and the formula is adjusted to maximize equivalence of the two groups.

The independent evaluators (IEs) who conduct diagnostics at baseline and follow-up visits will have separate calendars and channels of contact from the therapists and coordinators. Assignment of therapist will be based upon mutual alignment of schedules of the adolescent and therapist. When more than one therapist is available in an aligned slot, therapist caseload and adolescent preference (male or female therapist) will be taken into consideration. IEs who complete evaluations (for presence of mood disorder, mood symptoms) after the assessment period will remain blinded to treatment. We will report the extent to which this is successful, and the proportion of post-treatment evaluations that are conducted by blinded IEs.

IEs will administer the intake baseline assessment, the post-treatment assessment (16-20 weeks following baseline), as well as subsequent 12 month post-intervention follow-up interviews. Between the baseline and post-treatment assessment, adolescents will additionally report bi-weekly RRS measurements that are not shared with the therapist. To avoid accidental unblinding of IEs, a research assistant will meet with the participant and legal guardian prior to each diagnostic evaluation, in order to remind them of the importance of not disclosing this information to their assessor. Fidelity of blinding will be monitored with a blindness questionnairecompleted by IEs during follow-up assessments as noted above.

There is a detailed protocol to address suicidal ideation and risk, in which further questions are used to ascertain risk and appropriate actions are taken including consulting with supervisor, discussing with family, contacting crisis resources, or inpatient hospitalization. The trial also has a trained adolescent psychiatrist as independent study monitor to evaluate and address any safety issues.

### Interventions

Following a pilot study [69], remitted MDD adolescents will be randomised to AO as a comparison to RFCBT (Stage 1 of the trial). This is because RFCBT is not a common treatment in use in clinical settings, and has not previously been used in clinical trials of adolescents with remitted depression. This initial phase will therefore establish that RFCBT is effective in reducing rumination and changing the rs-fMRI connectivity of neural networks as predicted in this population. This comparison will additionally provide clinical decision metrics on who will benefit the most from RFCBT, which can be taken forward to refine the treatment protocol for Stage 2, in which RFCBT is compared to relaxation. All participants, regardless of arm, will receive one session of practice in progressive muscle relaxation, before progressing to RFCBT or AO.

Adolescents randomised to RFCBT will meet with a therapist on a typically weekly basis for 45-60 min following the manualized intervention for a target of 10 to 14 sessions [78], typically over a 3 month period. Rumination is characterized by abstract thinking about the causes, meanings, and implications of symptoms and difficulties, as exemplified by asking “Why me?” questions, with this abstract thinking implicated in the negative consequences of rumination. In contrast, encouraging more concrete thinking, focused on how events happen and the context and sequence of what did happen can help an individual move into a specific action and plan, keep an event in perspective, and reduce depression. RFCBT targets rumination and other maladaptive forms of emotion regulation such as suppression and avoidance and provides skills training in effectively coping with rumination. RFCBT specifically addresses rumination through psychoeducation, adopting a functional analytic approach to the learned habitual behaviour of rumination, and a focus on shifting processing style [79–81]. The adolescent is taught to notice triggers for rumination as well as the consequences of rumination and how to shift into practicing a more adaptive strategy such as an attention training exercise, behavioural activation, thinking in a concrete way, self-compassion, or active problem-solving [79–81]. RFCBT directly teaches adolescents to recognize rumination and to notice the influence this behavior has on their mood. The acronym ASK is used to teach adolescents that, rather than ruminating, which tends to take the form of passive, abstract, and critical forms of thinking about oneself, to be Active, Specific, and Kind. Through regular functional analyses in sessions, adolescents learn about their cycle of emotions and how the habit of rumination can make it harder to take action. A key skill taught is to change abstract and general thinking about difficulties and problems into a more specific, concrete and contextualized approach. Patients are taught to spot their abstract overgeneralized thoughts and “Why?” questions and to replace these with more helpful “How?” questions. Consistent with changing a habit, adolescents repeatedly practice using these different techniques in response to their warning signs for rumination (IF-THEN strategic plans) [82, 83].

Trial therapists will be psychologists and masters-level therapists who have completed a minimum of 5 days of training in RFCBT with EW and [name], (the treatment author and PI of the pilot adolescent trial), over 4 separate sessions, and will receive weekly supervision sessions from the treatment author and expert supervisors throughout the intervention delivery, including direct audio or video review of sessions. Therapists will use individual session templates to record and track therapy content and ensure adherence to the treatment protocol (including session checklists and overall therapy adherence module checklists). Digital recordings of therapy sessions will be used for the purposes of clinical supervision and monitoring. Twenty percent of sessions will be randomly reviewed using an adapted version of the Cognitive Therapy Rating Scale [84], modified for the specific principles and techniques of RFCBT, by an independent rater blind to treatment progress in order to monitor fidelity.

Participants will be provided with paper handouts and electronic tablet devices that are set-up with access to the therapy and homework materials. These (or the individuals’ cell phones) will additionally deliver personalised prompts to complete an electronic therapy diary (through the PACO Survey application), in order to monitor homework practice and track the relationships between practice of therapy techniques and levels of rumination in everyday life.

TAU may occur during the course of the trial with the participant’s primary care physician, mental health service provider, or psychiatrist, including a referral resource list that is provided to every participant for emergency and outpatient mental health services. TAU received will be assessed at the follow-up assessments. The primary treatments provided in this age range are expected to be supportive therapy and medication management (we expect roughly half will be on stable medication).

In the second (R33) stage of the trial, relaxation training will occur parallel to RFCBT to control for the effects of therapy structure, time, therapist contact, use of an active coping strategy for mood modulation, and attention. As such, sessions will occur weekly for 45-60 min and will include progressive muscle relaxation, simple breathing techniques, and guided imagery that focus on bodily and somatic relaxation. Adolescents randomized to relaxation will also receive exercises to do as homework in between sessions, parallel to the RFCBT group. This includes adaptions of relaxation formats for different situations that may not allow for a full execution (e.g., an airplane runway, in an office chair). Given that relaxation techniques are empirically supported for alleviating distress, anxiety, and depression among many different populations, we expect some effect of relaxation but it does not specifically target the mechanism of rumination.

### Outcomes

Outcomes will be assessed from baseline (pre-randomisation) to 16-20 weeks and 12 months post-intervention (see Fig. 1).

#### Primary outcome

The primary treatment outcome is self-reported reductions in rumination, as assessed using the brooding scale of the RRS [36] from baseline to 16-20 weeks post-baseline. Brooding is defined as “passive and judgmental pondering of one’s mood” ([85], p. 99), and is associated with maladaptive strategies and depression. We will use the Reliable Change Index (RCI) as an indication of change in brooding rumination scores [86]. RCI is a measure of how much change in a measurement can be ascribed as a meaningful movement at a statistical level, for the individual case, based upon the error inmeasurement, reliability of an instrument, and moderating for the effects of regression to the mean. In pilot work with adolescents, 57% of those treated with RFCBT obtained a change in total rumination scores at or above an RCI level, suggesting an adequate dose of targeted therapy (vs. 14% of AO group, e.g., random reduction).

The primary brain target (capturing the neural mechanisms compensating for rumination as a result of RFCBT) is elevated connectivity between the DMN and CCN (and diminished within-CCN connectivity) during rs-fMRI [46, 87]. Resting state fMRI (rs-fMRI) will investigate concurrent (or synchronized) changes in blood flow while adolescents are at rest with eyes open looking at a fixation cross. All adolescents will complete two identical MRI scans: at baseline and then at post-intervention (16 weeks), corresponding to the end of RFCBT sessions. A 64-channel coil will be used, and rs-fMRI sequences will be consistent with the Adolescent Brain Cognitive Development (ABCD) study protocol, with same TR, TE, and multiband sequences. We will collect 4 rs-fMRI runs at each of the two scans. Seed-based analyses will be used to probe changes to functional connectivity. The primary neural outcome is therefore reduced rs-fMRI connectivity between the left posterior cingulate cortex and right inferior frontal gyrus (nodes within the DMN and CCN respectively) [57]. Network-based analysis will also be probed for CCN-DMN changes in connectivity. Two experimental task-based paradigms [63, 88] will be employed to investigate directed induced rumination vs. distraction (block design), and uninstructed use of rumination during a sustained attention task [63]. These probes are explicitly designed to look at network function and dynamics of DMN nodes alone and with CCN, and how they may change selectively with RFCBT.

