**Method:**

This is a phase III two-arm, two-stage, RCT of depression prevention. The trial tests whether RFCBT reduces identified risk factors for depressive relapse (rumination, patterns of neural connectivity, and depressive symptoms) in adolescents with partially or fully remitted depression and elevated rumination. In the first stage, RFCBT is compared to treatment as usual within the community. In the second stage, the comparator condition is relaxation therapy. Primary outcomes will be (a) reductions in depressive rumination, assessed using the Rumination Response Scale, and (b) reductions in resting state functional magnetic resonance imaging connectivity of DMN (posterior cingulate cortex) to CCN (inferior frontal gyrus), at 16 weeks post-randomization. Secondary outcomes include change in symptoms of depression following treatment, recurrence of depression over 12 months post-intervention period, and whether engagement with therapy homework (as a dose measure) is related to changes in the primary outcomes.

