### Sample size

This trial was funded as the first stage (R61 grant) in a potential two-stage study, with the second stage (R33 grant) comparing RFCBT to an active control of relaxation therapy. Moving to the second stage is contingent on the first stage meeting the Go criteria of baseline to post-intervention between-treatment arm effect size changes of .5SD (effect size) in RRS and .5SD (effect size) in rs-fMRI connectivity from left PCC to right IFG. These effect sizes were chosen to reflect a noticeable clinical difference, necessary to progress to second stage. For this stage, the target recruitment is *n* = 30 per group. Power was computed using gPower 3.1 for a repeated measurements model in the first stage (R61), to compare the effects of RFCBT versus TAU + AO where observations are nested within subjects, targeting a .5SD (effect) size change, and with known reliability of RRS (*r* = .77) and rs-fMRI connectivity of left PCC to right IFG (*r* = .71). On this basis, a target recruitment of *n* = 30 per treatment arm is estimated to provide power of .99 for RRS and .98 for rs-fMRI. Assuming up to 15% follow-up attrition at post-intervention follow-up, power remains >.94 for both comparisons. For the R33 stage, there will be an active treatment comparator so the effect size difference is likely to be smaller. To achieve adequate power to detect a meaningful clinical difference, we assumed a minimum difference of 0.22 SD for each comparison; for power at 0.80, alpha at 0.05, assuming 15% follow-up attrition, we need to recruit 60 young people per treatment arm (*N* = 120).

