#### Secondary outcome

The occurrence and time to onset of any subsequent mood disorder and/or depressive episode are secondary outcomes. Recurrence of MDD and related mood disorders will be assessed by diagnostic interview (KSADS-PL) administered by IEs at post-intervention and at 12 months.

Dose is a rating of homework completion and skill integration (rated by the clinician), and degree of rumination change (defined by RCI). The primary clinical outcome is therefore change on the RRS score (as captured by the RCI) after treatment. We will additionally examine the stability of RRS change at 6 and 12 months post-intervention.

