
### Statistical methods

Primary analyses will be conducted on intention-to-treat basis (as randomised) and missing data assumed to be missing at least at random (MAR), confirmed using missing data analysis. Unplanned missing data will be handled via multiple imputation (MI). Secondary variables will be used to improve the estimation of missing data. Sensitivity analysis, assuming a variety of MI models (Missing at Random; Missing Not at Random), will confirm the probable impact of missing data.

To compare the effects of RFCBT with the control arm, mixed-effects longitudinal models will be used. The first analysis tests change in RRS scores; the second analysis tests change in connectivity between the left posterior cingulate cortex and right inferior frontal gyrus. For each, the random subject intercept parameter will explain the variation in measurements of subjects at baseline, whereas the random slope parameter will explain variation over time. The models will also incorporate within-subject variation. The group by time interaction parameter will be used to differentiate the trend of RFCBT from that of the control arm on each outcome. Sustainability of improvement will be measured utilizing data from post-intervention to until 12 months post-intervention. To measure relation between degree of daily engagement in homework and degree of reduction in rumination, we will calculate Pearson correlations. A contrast using pre and post measures of rs-fMRI between left PCC and right IFG in adolescents on the RFCBT arm will be compared to the control arm, as described in Jacobs et al. 2016 [57]. The same approach will be adopted for exploratory, task-based fMRI, capturing state rumination.

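### The primary rumination outcome is stated inconsistently (RRS score, RRS brooding scale, RRS change captured by the RCI), so the primary test and the rumination half of the Go rule rest on an unsettled variable

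*Protocol article*

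**What the plan says.** All references are to the protocol article.

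- **Abstract, Method:** the first primary outcome is "reductions in depressive rumination, assessed using the Rumination Response Scale", with no subscale named.
- **Sample size:** the rumination part of the Go criterion is "baseline to post-intervention between-treatment arm effect size changes of .5SD (effect size) in RRS". Power is computed "targeting a .5SD (effect) size change" with a reliability of .77 attributed to the RRS. No reliability is given for brooding.
- **Primary outcome:** "The primary treatment outcome is self-reported reductions in rumination, as assessed using the brooding scale of the RRS". It continues: "We will use the Reliable Change Index (RCI) as an indication of change in brooding rumination scores". The supporting pilot evidence is on a different score: "57% of those treated with RFCBT obtained a change in total rumination scores at or above an RCI level", against 14% of the assessment-only group.
- **Secondary outcome:** "The primary clinical outcome is therefore change on the RRS score (as captured by the RCI) after treatment". The sentence before it makes RCI-defined rumination change one component of dose.
- **Statistical methods:** "The first analysis tests change in RRS scores", by a mixed-effects model with a group-by-time interaction.

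The time point varies slightly too. The abstract puts it at 16 weeks after randomisation, while the Aims and the Primary outcome section use 16 to 20 weeks after baseline.

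**The concern.** These are conflicting positive statements, not detail left to an analysis plan. No analysis plan can follow both the Primary outcome and the Secondary outcome sections as written. The pilot sentence shows that the authors treat total and brooding scores as distinct.

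Three things are at stake. First, the variable in the primary test is open, so it could be settled after the data are seen. Second, progression to stage 2 (120 participants) needs a .5 SD difference in RRS, and the scale that supplies it is not fixed. Third, the .77 reliability and the power built on it hold only for the scale they came from.

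The RCI adds a further ambiguity. Read as a graded index it changes little. Read as a responder cut-off it is a much less efficient endpoint. Using RCI-defined rumination change within dose also makes one quantity both outcome and exposure. Any relation between dose and rumination change would then be partly built in.

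**Working it through.** **1. Which variable is used where**

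| Section | Rumination variable |
|---|---|
| Abstract | RRS |
| Sample size (Go rule, power) | RRS, r = .77 |
| Primary outcome | RRS brooding scale, with RCI on brooding |
| Primary outcome (pilot support) | total rumination, at or above an RCI level |
| Secondary outcome | RRS score, captured by RCI |
| Statistical methods | RRS scores, mixed model |

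**2. The plan's own power figure.** The article states .99 for the RRS at 30 per arm. The within-between interaction with two time points, f = .25, N = 60 and r = .77 has noncentrality f²·N·m/(1 − r) = .0625 × 60 × 2/.23 = 32.6. Power is above .99, in line with the article.

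For a true between-arm difference of .5 baseline SD in change, the SD of change is √(2(1 − .77)) = .678. The standardised difference is .5/.678 = .737, and the noncentrality is .737² × 30/2 = 8.15. Power is .80. The first noncentrality is four times the second, so f = .25 corresponds to a 1.0 SD difference in change. That gap is a separate matter. It is shown here only to explain why .80, not .99, is the comparator below.

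**3. If the RCI were a responder cut-off.** Assumptions, not stated in the article:
- cut-off of 1.96 times the SD of change
- normal change scores
- pre-post correlation equal to the stated .77
- two-sided .05
- 30 per arm
- true .5 SD difference in change

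The cut-off is 1.96 × .678 = 1.33 baseline SD. For a control rate p0, the treated rate is P(Z > z(p0) − .737), where z(p0) is the upper p0 point of the normal distribution.

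| Scenario | Rates | Fisher | Chi-square, uncorrected |
|---|---|---|---|
| No mean change in controls | 11.1% v 2.5% | .06 | .24 |
| Pilot control rate, .5 SD effect | 37% v 14% | .42 | .53 |
| Pilot rates in both arms | 57% v 14% | .92 | .95 |
| Continuous change, .5 SD effect | – | – | .80 (t-test) |

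The 57% v 14% row is a much larger effect than the planned one. Under the same assumptions it implies a difference of about 1.26 SD of change, or 1.26 × .678 = .85 baseline SD.

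**4. If the scale is brooding.** Its reliability is not given. Over an assumed .60 to .85, power for continuous change at a .5 SD difference runs from about .57 to .94, so the figure for the RRS does not carry over.

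**5. Can the choice of scale change the Go result?** For illustration, suppose the true effect is exactly .5 SD on both scales, so that each passes half the time. Suppose also that the two estimated differences correlate at ρ. The chance that they fall on opposite sides of the threshold is arccos(ρ)/π. This is .927/3.142 = .30 at ρ = .6 and .451/3.142 = .14 at ρ = .9. The correlations are assumed. The disagreement is smaller when the true effect lies away from the threshold.

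**The case against.** The strongest reply is that Statistical methods already fixes one rumination analysis, a mixed model on RRS scores, and that the RCI is only described as an indication of change. Much of this stands, and it rules out several stronger readings.

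- **Almost no power.** A reader might infer this from an RCI-based primary. It is true only with no mean change in controls and a Fisher test. With the pilot's control rate power is about one half, and at the pilot rates it exceeds .9.
- **A responder test is planned.** No section states a between-arm comparison of RCI proportions. A continuous RCI is a linear rescaling of change and loses no power. The threshold wording is attached to the pilot data. The article also says its RCI allows for regression to the mean, so the 1.96 formula used above may not be the one intended.
- **The Go decision depends on the RCI.** As written it does not. It is an effect size in RRS, so only the full score versus brooding is open.
- **Inflated false-positive rate from trying all versions.** The article plans one rumination analysis and does not propose testing several.
- **RRS total is the only reading.** The abstract, Sample size and Statistical methods name the instrument but never say total. The one section that specifies a scale for the primary outcome names brooding.
- **Timing.** Most sections agree on 16 to 20 weeks, and nothing suggests that the window differs by arm. This is a wording correction.

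The reply does not settle which RRS score enters the mixed model and the Go rule, or what the RCI does in the definition of the primary clinical outcome.

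**Conclusion.** The inconsistency is real and needs correcting, because it concerns the primary variable and half of the Go rule. What is unresolved is the full RRS versus brooding for the test, the Go criterion and the planning reliability, together with an undefined role for the RCI.

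The power loss is conditional. It arises only if the RCI is used as a cut-off, and then power at the planned effect falls from about .80 to .42–.53 (14% control rate) or .06–.24 (no control change), under the assumptions listed in the working. It is not a defect of the mixed model that the article actually specifies. The placing of RCI-defined change inside dose is a smaller but definite fault.

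**What to change.** Before unblinding:

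1. Name one continuous RRS variable as the single primary rumination outcome, and use it in the abstract, outcome section, Go rule, power statement and mixed model. There are two acceptable routes: RRS total, with brooding secondary; or brooding, with the power statement and Go rule restated using brooding's own reliability.
2. Remove the reference to the RCI from the definition of the primary clinical outcome. Report RCI response as a secondary, descriptive outcome, with its formula and cut-off given.
3. Define dose by homework completion and skill integration, without rumination change.
4. Align the abstract's time point with the window of 16 to 20 weeks after baseline.

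The cost is wording in the protocol and registry, plus a short recalculation if brooding is chosen. No new data are needed, since every version comes from the same questionnaire.
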